#### 2.1.1 PRINCIPAL INVESTIGATOR'S QUALIFICATIONS & AGREEMENTS

1. The investigators should be qualified by education, training, and experience to assume responsibility for the proper conduct of the trial at their site and should provide evidence of such qualifications through an up-to-date curriculum vitae and/or other relevant documentation requested by the Sponsor, the REC, the IRB, and/or the regulatory authority(ies).
2. The investigators should be thoroughly familiar with the appropriate use of the investigational products as described in the protocol, in the current Investigator Brochure, in the product information and in other information sources provided by the Sponsor.
3. The investigators should be aware of, and should comply with, the principles of GCP and the applicable regulatory requirements. A record of GCP training should be accessible for all investigators.
4. The investigators/site should permit monitoring and auditing by the Sponsor, and inspection by the appropriate regulatory authorities
5. The investigators should maintain a delegation log of appropriately-qualified persons to whom the Principal Investigator has delegated significant trial-related duties.
6. The Principal Investigator should sign a Principal Investigator statement, which verifies that the investigators at their site are willing and able to comply with the requirements of the trial.

#### 2.1.2 ADEQUATE RESOURCES

1. The investigators should be able to demonstrate a potential for recruiting the required number of suitable subjects within the agreed recruitment period.
2. The investigators should have sufficient time to properly conduct and complete the trial within the agreed trial period.
3. There should be available an adequate number of qualified staff and adequate facilities for the foreseen duration of the trial to conduct the trial properly and safely.
4. The Principal Investigator should ensure that all persons assisting with the trial are adequately informed about the protocol, the investigational product(s), and their trial-related duties and functions.
5. The site should have sufficient data management resources to allow prompt data entry and return of resolved queries to MRC/UVRI and LSHTM Uganda Research Unit (refer to the Data Management Plan for timelines).

### **2.1.3 SITE ASSESSMENT**

Each selected clinical trial site must complete the PrEPVacc Evaluation Form. The Investigator Statement verifies that the site is willing, and able to comply with the requirements of the trial. This will be signed by the Principal Investigator at the site. In addition and in compliance with the principles of GCP, all site staff participating in the trial must complete the Signature and Delegation of Responsibilities Log and forward this to MRC/UVRI and LSHTM Uganda Research Unit. MRC/UVRI and LSHTM Uganda Research Unit must be notified of any changes to trial personnel and/or their responsibilities.

## **2.2 SITE/INVESTIGATOR EXCLUSION CRITERIA**

It is necessary to recruit a trial population with an HIV incidence in the region of 4/100 person years. Participation will be determined by the PrEPVacc Trial Steering Committee on review of the incidence in the Registration Cohort and sites with low incidence will not be able to take part in the PrEPVacc trial. The target sample size for each site will be determined by the incidence observed in the Registration Cohort or equivalent studies.

## **2.3 APPROVAL AND ACTIVATION**

On receipt of the above essential documents, written confirmation will be sent from MRC/UVRI and LSHTM Uganda Research Unit to the Principal Investigator (PI), and study specific training will be organised. This will include training on the database, randomisation and unblinding procedures as well as the management and reporting of adverse events. The coordinating team will also visit the site pharmacist to go through the pharmacy procedures and documents.

When everything is in place, including a completed Delegation Log the site will be activated and vaccines and drugs dispatched to the named pharmacist in the Accreditation form documents.

1. The site should conduct the trial in compliance with the protocol as agreed by the Sponsor, by the regulatory authority (ies), and by the REC and institutional IRB that gave a favourable opinion.
2. The PI or delegate should document and explain any deviation from the approved protocol, and communicate this with the trial team at MRC/UVRI and LSHTM Uganda Research Unit

### 3 SELECTION OF PARTICIPANTS

There will be **no exceptions** to eligibility requirements at the time of randomisation. Questions about eligibility criteria should be addressed prior to attempting to randomise the participant. Additional guidance can be found in the Study Operations Manual (SOM) and CRF, for a list of highly effective contraception and what would put volunteers who have systemic disease at screening or enrolment at risk, preclude vaccination or compromise immune responses.

The eligibility criteria are the standards used to ensure that only medically appropriate participants are considered for this study. Participants not meeting the criteria should not join the study. For the safety of the participants, as well as to ensure that the results of this study can be useful for making decisions regarding other participants with similar needs, it is important that no exceptions be made to these criteria for admission to the study.

Participants will be considered eligible for enrolment in this trial if they fulfil all the inclusion criteria and none of the exclusion criteria as defined below.

#### 3.1 PARTICIPANT INCLUSION CRITERIA

1. HIV uninfected adults aged between 18 and 40 years on the day of screening
2. Willing and able to provide informed consent prior to participation
3. Willing and able to comply with the visit schedule and provide blood, urine and other samples at the required time points
4. Home address accessible for visiting and intending to remain within the recruitment area for at least 82 weeks from screening
5. Likely to be at risk from exposure to HIV during follow up
6. Willing to undergo HIV testing, receive HIV test results and risk reduction counselling which includes promotion of PrEP and condoms
7. If female, of child-bearing age and not sterilised, willing to use a highly effective method of contraception from screening until 18 weeks after the last injection
8. If male and not sterilised, willing to avoid impregnating female partners from screening until 18 weeks after the last injection

#### 3.2 PARTICIPANT EXCLUSION CRITERIA

1. HIV infection or indeterminate HIV result at screening or enrolment
2. Hepatitis B surface antigen positive
3. If female, currently pregnant (evidence from positive serum or urine pregnancy test), or lactating
4. Participating in another biomedical research study or in receipt of a live vaccine within 30 days prior to randomisation
5. Participation in a previous HIV vaccine or HIV immunotherapy trial
6. Receiving blood products or immunoglobulins within 12 weeks of screening
7. Known hypersensitivity to any component of the vaccine formulations used in this trial or history of severe or multiple allergies to vaccines, drugs or pharmaceutical agents
8. Presence of a systemic disease at the time of randomisation or history of chronic illness that in the opinion of the investigator may compromise the participant's safety, preclude vaccination or compromise an immune response to vaccine

9. Abnormalities in routine laboratory parameters (Hb, creatinine, AST/ALT, alkaline phosphatase, total Bilirubin and glucose) of Grade 2 and above using the DAIDS toxicity table, version 2.1 July 2017 or estimated glomerular filtration rate less than 60ml/min

### **3.3 NUMBER OF PARTICIPANTS**

The target accrual for the final vaccine analysis is a minimum of 1668 HIV uninfected adults aged 18 – 40 years from participating centres in sub-Saharan Africa, but this is an endpoint driven MAMS trial design and therefore the target may be adjusted following a recommendation from the IDMC ([Section 9.4](#)). Also, if a participant stops trial follow-up before they have completed the first 3 injections, another participant will be randomised whilst there is sufficient product and provided enrolment is ongoing.

### **3.4 CO-ENROLMENT GUIDELINES**

Participants should not be participating in any other biomedical research study within 30 days prior to randomisation, nor should they co-enrol into any other interventional studies that might impact on the primary or secondary outcomes for the duration of their participation in the PrEPVacc trial.

### **3.5 SCREENING PROCEDURES & PRE-RANDOMISATION INVESTIGATIONS**

Written or witnessed informed consent to enter into the trial and be randomised must be obtained from participants, after explanation of the aims, methods, benefits and potential hazards of the trial and BEFORE any trial-specific procedures are performed or any blood is taken for the trial (see Template Participant Information Sheet and Consent Form). Consent will be taken for participation in any sub -studies (including additional sample storage).

It must be made completely and unambiguously clear that the participant is free to refuse to participate in all or any aspect of the trial, at any time and for any reason, without incurring any penalty or affecting their treatment in future.

Signed consent forms must be kept by the investigator and documented in the case report form (CRF) and a copy offered to the participant. If the participant does not wish to take the copy, this should be documented in their clinic notes and the copy should be filed with the investigator copy.

See [section 6.2](#) for details of screening procedures.

## 4 REGISTRATION & RANDOMISATION

Before randomisation, the participant's eligibility must be confirmed by completing the screening CRFs. All blood tests must be available to confirm that the participant is eligible in terms of laboratory criteria.

### 4.1 RANDOMISATION PRACTICALITIES

Further details on the process of randomisation can be found in [Sections 6.3 and 9.1](#).

**RANDOMISATIONS**  
To randomise,  
Details to be added when available

Randomisation will be web-based with a manual randomisation process to cover any instances when access to the internet is not possible. This will be detailed in the SOM. In brief, a single code per participant will be generated electronically to inform pharmacy which vaccine group the participant is allocated to, and which PrEP allocation (TAF/FTC or TDF/FTC).

### 4.2 RANDOMISATION CODES & UNBLINDING

Randomisation codes and unblinding are considered in [Section 5.6](#).

Study staff and participants will not know who has been allocated vaccine and who has been allocated placebo, but it is not possible to blind staff to the difference in volume as they will be administering 1ml in one arm and 0.45ml in the other at the same timepoint on four occasions (see section 5.3.6). Study staff will therefore be able to identify who has been randomised to the schedule that includes gp140 in MLPA-L or its matched placebo.

Allocation to the vaccine regimens will be in the ratio of 1:1:1 for groups A:B:C respectively. As the volume of the recombinant proteins differs between the two active arms, the placebo injection will be further divided 1:1 to 1ml: 0.45ml in order to ensure that staff administering the injection cannot differentiate between active and placebo.

As the trial is adaptive, the ratio may change to 1:1 during the trial if one of the vaccine regimens is discontinued or temporarily paused due to an issue with one of the products. If this is necessary, a new randomisation database will be implemented with the new list and the previous database archived after completing the quality checks.

The pharmacist at each centre will know the precise allocation throughout the trial as they will have a list that is mapped to each randomisation list

The randomisation to control PrEP:experimental PrEP is 1:1 and all study staff and participants will know the allocation after randomisation as this is open-label.

## 5 TREATMENT OF PARTICIPANTS

### 5.1 INTRODUCTION

The trial treatments in this trial are two different active combination HIV vaccine regimens, using products that are not licensed, saline placebo, and two different oral PrEP drugs both of which are licensed for treatment of HIV infection, and for prevention in some populations in some countries.

The vaccine products will need to be drawn up by the pharmacist who will have access to a list matching the trial identifier to the allocated regimen. Two vaccine products will be administered at each of four timepoints. They will be injected intramuscularly into the deltoid muscle of each upper arm, with DNA, MVA or matched placebo in the left arm and recombinant protein or matched placebo in the right arm.

The PrEP tablets will be dispensed by study staff in an open-label manner at three to four timepoints, and additional timepoint to top up supply if required.

The treatment schedule is outlined in table 6 below:

**Table 6: Vaccine and PrEP candidates, placebo and PrEP control, and dispensing Schedule**

| Visit Schedule
Target week         | Visit 2
Week 0                  | Visit 4
Week 4                  | Visit 7
Visit 4 +12wks | Visit 8
Visit 4 + 20wks    | Visit 12
Visit 8 + 24 wks  |
|---------------------------------------|------------------------------------|------------------------------------|---------------------------|-------------------------------|-------------------------------|
| Group A
Vaccine combination | DNA-HIV-PT123
AIDSVAX® B/E      | DNA-HIV-PT123
AIDSVAX® B/E      |                           | DNA-HIV-PT123
AIDSVAX® B/E | DNA-HIV-PT123
AIDSVAX® B/E |
| Group B
Vaccine combination | DNA-HIV-PT123
CN54gp140 +MPLA-L | DNA-HIV-PT123
CN54gp140 +MPLA-L |                           | MVA
CN54gp140 +MPLA-L      | MVA
CN54gp140 +MPLA-L      |
| Group C
Placebo control     | N/saline                           | N/saline                           |                           | N/saline                      | N/saline                      |
| PrEP Candidate
TAF/FTC      | 60 tablets                         | 90 tablets                         | +/-30 tablets             | If required                   |                               |
| PrEP Control
TDF/FTC        | 60 tablets                         | 90 tablets                         | +/-30 tablets             | If required                   |                               |

Additional detail regarding the treatments to be given in this trial is provided in the IBs for unlicensed products or SPC for licensed products, the study SOM and Local Pharmacy Working Instructions.

### 5.2 COMBINATION GROUP A

#### 5.2.1 DNA-HIV-PT123

DNA-HIV-PT123 candidate HIV vaccine is released by Ajinomoto Althea Inc, San Diego, US in accordance with GMP and provided by the EuroVacc Foundation, Lausanne, Switzerland.

DNA-HIV-PT123 is supplied as a 4 mg/mL DNA solution in a 2 mL sterile glass vial containing a volume to deliver 1 ml of a clear, colourless, sterile isotonic solution. Each vial is in an individual secondary packaging. Vials and packaging are labelled according to GMP.

### 5.2.2 AIDSVAX® B/E

The AIDSVAX® B/E vaccine was originally developed by Genentech, Inc., and is now being provided by Global Solutions for Infectious Diseases.

AIDSVAX® B/E is supplied as a sterile suspension in single-use glass vials containing a volume to deliver 1mL of MN rgp120 and A244 rgp120/HIV protein (300mcg each) adsorbed onto a total of 600 mcg aluminium as aluminium hydroxide gel suspension as adjuvant. Vials and packaging are labelled according to GMP.

### 5.2.3 TREATMENT SCHEDULE

The target is a minimum of 556 individuals who complete the schedule, and so participants who drop out before the third injection timepoint will be replaced by randomising another eligible volunteer. Therefore up to 620 individuals could receive this combination.

Participants randomised to Schedule A will receive DNA-HIV-PT123 vaccine and AIDSVAX® B/E protein as described in [Table 6](#) at visits 2, 4, 8 and 12.

### 5.2.4 DOSE AND ADMINISTRATION

1ml of DNA-HIV-PT123 will be injected into the deltoid muscle of the left upper arm using the appropriate needle and in accordance with the SOM. Study staff should inject the same arm on each of the four occasions.

1ml of AIDSVAX® B/E will be injected into the deltoid muscle of the right arm using the appropriate needle and in accordance with the SOM. Study staff should inject the same arm on each of the four occasions.

In the event that study staff administer the product into the opposite muscle to the one intended a deviation should be noted (see SOM for details) and revert to the correct arm for any remaining vaccinations.

### 5.2.5 STORAGE

The vaccines will be stored at the following conditions according to the SOM and Local Pharmacy Working Instructions that will be reviewed at site initiation. They will be stored in a secure, limited access storage area under the specified storage requirements:

- ▶ DNA-HIV-PT123 must be stored at -20°C±5°C.
- ▶ AIDSVAX® B/E must be kept refrigerated (2° to 8°C).

### 5.2.6 DISPENSING

The PI will ensure that the vaccines are dispensed in accordance with the protocol, the study specific SOM and Local Pharmacy Working Instructions as appropriate. The study pharmacist of the respective site will be responsible for preparing the injection syringes in accordance to the SOM. The syringe will be labelled with “Name of Study Product/placebo” with an overlay to maintain blinding (detailed label design will be defined in the SOM). Local Pharmacy Working Instructions will be reviewed at site initiation.

Accountability Logs will be kept to record the identification of the participant to whom the vaccine was dispensed and the date. Any damaged or unused vials will also be documented. The log will be checked during monitoring visits and at the end of the trial.

### 5.2.7 DOSE MODIFICATIONS & INTERRUPTIONS

There are no planned modifications to dose, other than interruption and discontinuation (see [sections 5.7 and 9.4](#) for details of discontinuation). This applies to all of the vaccine products.

The schedule may be interrupted if a participant has symptoms or signs on the day of scheduled injection, and the investigator considers it best to defer the injection. Such a decision should be taken in consultation with the PI. The participant will be asked to return for review within the window period

of the scheduled injection. Provided the injection is administered during the window period outlined in the paragraph below for missed visits, this will not be a protocol deviation.

The participant may not be well enough within the ideal window period, or may not be able to attend in this timeline for reasons outside their control. Study staff should consult the SOM to find out whether they can proceed with the injection or need to contact the TSG by email ([PrEPVacc\\_trial\\[contact]](mailto:[contact])). The site PI should consult with the TSG (see [section 14.2](#)) regarding further injections and the schedule to follow thereafter. Protocol deviations will be recorded in the appropriate CRF.

In the event that there is a confirmed (1) grade 3 or worse solicited adverse event that has persisted for more than 72 hours, regardless of relationship or (2) other grade 3 or worse adverse event that is possibly, probably or definitely related to vaccine, the PI or deputy should interrupt the vaccine schedule and inform MRC/UVRI and LSTHM within 24 hours using the TSG email (see [section 7](#)). The event will be reviewed by the TSG for an opinion regarding resuming the vaccine schedule, pending further investigation of the event. It may be necessary to consult an independent clinical expert with expertise in the disease area relevant to the adverse event. Such an interruption will be considered a protocol-planned interruption.

As this is a trial with combination vaccine regimens, one of the active regimens may need to be interrupted temporarily if there is a quality issue with any one product that requires further investigation. Enrolled participants will not receive any further injections with this product, and the matched placebos will be managed in the same way in order to maintain the blind between active/placebo. Participants will be informed verbally at the next visit, and in writing after approval from the appropriate ethics committee. If the product under investigation is required at enrolment in one combination arm only, a second randomisation database and list will be implemented to allow enrolments to continue to the other combination arm and placebo in a 1:1 ratio. Once resolved and the other combination arm and matched placebo can be resumed, a third randomisation database and list will be implemented to return to a 1:1:1 ratio. If the product under investigation is DNA-HIV-PT123, all enrolments will need to be paused.

## **5.3 COMBINATION GROUP B**

### **5.3.1 DNA-HIV-PT123**

See [section 5.2.1](#).

### **5.3.2 MVA-CMDR**

MVA-CMDR is developed by MHRP (United States Military HIV Research Program), and manufactured by Vibalogics GmbH in Germany according to the European Union regulations for GMP.

MVA-CMDR is presented as a frozen liquid formulation, which is thawed prior to injection and appears as a white to opaque, slightly to moderately cloudy liquid.

The vaccine is provided in sealed glass vials containing  $1 \times 10^8$  pfu/mL of product. Vials and packaging are labelled according to GMP.

This vaccine candidate is classified as a genetically modified organism (GMO) in South Africa and will be used in compliance with the applicable national regulations.

### **5.3.3 CN54gp140**

CN54gp140 is a recombinant envelope protein derived from a clade C HIV-1 isolate. CN54gp140 is manufactured by Polymun Scientific Immunobiologische Forschung GmbH, Klosterneuburg, Austria according to European GMP.

CN54gp140 drug product is a colourless soluble glycoprotein with no visible particulates. The vaccine is provided in Type I glass vials (3 ml) with a nominal concentration of 500µg/ml and containing a volume of 0.35ml. Vials and packaging are labelled according to GMP.

### 5.3.4 MPLA LIPOSOMES (MLPA-L)

Monophosphoryl Lipid A (MPLA), a widely used adjuvant, is a non-toxic version of LipoPolySaccharide (LPS), which is isolated from the LPS lipid A region of Salmonella Minnesota R595. In this study, MPLA is co-formulated with liposomes.

MPLA is purchased from Avanti Polar Lipids and formulated by Polymun in liposomes using cholesterol, DMPC and DMPG according to GMP. The MPLA-L formulation is presented as a milky white to opalescent suspension.

MPLA-L drug product is filled at a nominal concentration of 25µg/ml into Type I glass vials (3 ml) with fluoropolymer coated chlorobutyl rubber stoppers and flip-off plain aluminium overseals. Vials and packaging are labelled according to GMP.

### 5.3.5 TREATMENT SCHEDULE

The target is a minimum of 556 individuals who complete the schedule, and so participants who drop out before the third injection timepoint will be replaced by randomising another eligible volunteer. Therefore up to 620 individuals could receive this combination.

Participants randomised to Schedule B will receive DNA-HIV-PT123 vaccine and CN54gp140 combined with MPLA-L as described in [Table 6](#) at visits 2 and 4 and MVA vaccine and CN54rgp140 combined with MPLA-L at visits 8 and 12.

### 5.3.6 DOSE AND ADMINISTRATION

1ml of DNA-HIV-PT123 will be injected into the deltoid muscle of the left upper arm using the appropriate needle and in accordance with the SOM. Study staff should inject the same arm on each of the two occasions.

1ml (1x10^8 pfu) of MVA will be injected into the deltoid muscle of the left upper arm using the appropriate needle and in accordance with the SOM. Study staff should inject the same arm on each of the two occasions, and this should be the arm in which DNA-HIV-PT123 was administered.

In the event that study staff administer the product into the opposite muscle to the one intended a deviation should be noted (see SOM for details) and revert to the correct arm for any remaining vaccinations..

The pharmacist will withdraw 0.4mL of MPLA-L from the 3ml vial containing 0.55mL of MPLA-L and add this to the 3ml vial containing 0.35mL of CN54gp140. The vial contents will be mixed by gentle agitation and 0.45mL of will be withdrawn from the vial to make a concentration of 100µg CN54gp140 and 5µg MPLA-L and provided to study staff in a syringe in accordance with the SOM. The combined products will be injected into the deltoid muscle of the right arm using the appropriate needle and in accordance with the SOM. Study staff should inject the same arm on each of the four occasions.

As the volume of the CN54gp140 in MPLA-L is only 0.45ml and this differs from the volume being injected into the other arm(1ml), clinic staff will be aware that participants have been randomised to this arm or matched placebo.

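### The MPLA-L amount stated for the Group B protein injection does not follow from the protocol's own concentrations and mixing volumes (about 6 µg against 5 µg)

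*Protocol*

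**What the plan says.** Three sections of the protocol together define the content of the Group B protein injection.

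- Section 5.3.3 describes the CN54gp140 vial: "nominal concentration of 500µg/ml and containing a volume of 0.35ml".
- Section 5.3.4 gives the adjuvant strength: "MPLA-L drug product is filled at a nominal concentration of 25µg/ml".
- Section 5.3.6 gives the preparation. First, "The pharmacist will withdraw 0.4mL of MPLA-L from the 3ml vial containing 0.55mL of MPLA-L", then "add this to the 3ml vial containing 0.35mL of CN54gp140". After mixing, "0.45mL of will be withdrawn from the vial to make a concentration of" the stated content, "100µg CN54gp140 and 5µg MPLA-L and provided to study staff in a syringe".

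The 0.45 mL volume recurs in the summary table (Randomisation) and in sections 4.2, 5.4.1 to 5.4.3, 5.6 and 6.3.3. There it sets the volume of the matched placebo and explains what staff can and cannot infer about allocation.

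**The concern.** Section 5.3.6 gives both the recipe and its result, and sections 5.3.3 and 5.3.4 supply the strengths that connect them. A reader can therefore check the result, and the MPLA-L figure fails. The wording adds a smaller fault: 100 µg and 5 µg are amounts, yet the text calls them a concentration.

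This is the dosing instruction for one of the two experimental regimens, not background text. The injection is scheduled at visits 2, 4, 8 and 12 for at least 556 and possibly up to 620 people (section 5.3.5), so for at most 620 × 4 = 2,480 injections. At stake is whether the protocol says consistently what Group B received. A pharmacist working from the volumes and someone relying on the stated content would record different adjuvant amounts for the same syringe.

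**Working it through.** **Inputs, all from the protocol**

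- CN54gp140: 500 µg/mL, 0.35 mL in the vial (5.3.3; volume repeated in 5.3.6)
- MPLA-L: 25 µg/mL (5.3.4), 0.4 mL transferred (5.3.6)
- Volume withdrawn: 0.45 mL (5.3.6)
- Stated content: 100 µg CN54gp140 and 5 µg MPLA-L (5.3.6)

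**Attempt to reproduce the stated content**

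Formula: amount withdrawn = concentration × volume added ÷ total mixed volume × volume withdrawn.

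- Total mixed volume: 0.35 + 0.40 = 0.75 mL, of which 0.45 mL is 60%
- CN54gp140: 500 × 0.35 = 175 µg in the mixture; 175 × 0.60 = 105 µg withdrawn, against 100 µg stated (+5%)
- MPLA-L: 25 × 0.40 = 10 µg in the mixture; 10 × 0.60 = 6.0 µg withdrawn, against 5 µg stated (+20%)

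The stated pair is not reproduced.

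**Could a single changed figure explain it?**

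Each line below is a diagnostic, not a suggested preparation.

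| Figure allowed to vary | Value that gives 100 µg protein | Value that gives 5 µg MPLA-L |
|---|---|---|
| Volume withdrawn | 100 ÷ (175/0.75) = 0.429 mL (MPLA-L then 5.71 µg) | 5 ÷ (10/0.75) = 0.375 mL (protein then 87.5 µg) |
| CN54gp140 volume in the vial | 0.32 mL | 0.50 mL (protein then 125 µg) |
| MPLA-L volume transferred | 0.4375 mL | 0.28 mL |

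In every row the two amounts need different values. For the withdrawn volume the reason is simple. The mixture has a protein to MPLA-L ratio of 175:10 = 17.5:1, the stated content has 100:5 = 20:1, and withdrawing more or less does not change a ratio.

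Two other readings also fail. Adding the whole 0.55 mL of MPLA-L gives 87.5 µg and 6.88 µg in 0.45 mL. A 1:1 mixture gives 112.5 µg and 5.63 µg.

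**A more general check**

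At the stated strengths, 100 µg of protein occupies 100 ÷ 500 = 0.20 mL and 5 µg of MPLA-L occupies 5 ÷ 25 = 0.20 mL, together 0.40 mL. A 0.45 mL injection made only from these two products therefore cannot contain exactly both amounts, whatever volumes are mixed. At least one of the strengths, the injected volume or the stated amounts must be inexact.

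**The case against.** The strongest reply is that the strengths are nominal and the practical detail sits elsewhere. Section 5.3.6 defers to the Study Operations Manual, and sections 5.1 and 5.2.6 also point to local pharmacy instructions; neither document is shown. Some liquid may stay in the needle or syringe. The protocol gives no figure for this. If one assumes a loss of 0 to 0.05 mL, the delivered content runs from 105 µg and 6.0 µg (no loss) to 93.3 µg and 5.33 µg (0.40 mL delivered). At 0.41 mL delivered it would be 95.7 µg and 5.47 µg, which round to 100 and 5 at one significant figure.

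Part of this stands. The 5% protein gap is within rounding of a nominal strength and is not a finding by itself. The statement that no volume gives both amounts holds for exact equality only. The 20% is a difference between figures on paper, not a measured dose.

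It does not remove the contradiction. The protocol treats 0.45 mL as the volume injected, for example in section 6.3.3, and mentions no overfill, dead space or tolerance. At 0.45 mL, 6 does not round to 5. Further detail in a manual cannot make two figures in the protocol agree.

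It is also fair to say that the mixing volumes are given once and 0.45 mL is used consistently. Anyone who follows the recipe makes the same product for each Group B participant. The inconsistency lies in the content attributed to that product; nothing here bears on randomisation, the primary endpoint or the comparison with placebo.

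**Conclusion.** The contradiction is real. On the protocol's nominal figures the 0.45 mL Group B injection holds about 6 µg of MPLA-L, 20% more than the 5 µg stated, and about 105 µg of CN54gp140, which is compatible with a rounded 100 µg. No other part of the protocol reconciles the figures. The regimen that the trial will report for Group B is therefore not consistently defined.

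This rests on three assumptions: the nominal strengths hold, the vial holds the stated fill, and the full 0.45 mL is injected.

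A reader might infer more than this supports:

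- **That participants are given a fifth too much adjuvant.** This takes the stated amounts as correct and the volumes as wrong. The error could equally lie in a stated amount, a strength or a volume.
- **That safety reporting or comparison with earlier studies is compromised.** The reporting triggers in section 7 do not depend on micrograms of adjuvant. Table 4 lists one study with MPLA liposomes and gives no dose. The protocol offers no evidence that 1 µg of MPLA-L changes safety or immune response.
- **That dispensing should be held.** The documents give no basis for that. The point calls for reconciliation of the text.

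**What to change.** Check the strengths, the mixed volumes, the withdrawn volume and the stated amounts in sections 5.3.3, 5.3.4 and 5.3.6 against the product documents and the pharmacy instructions, and correct whichever figure is wrong. If an overfill, a loss allowance or rounding explains the gap, state it in section 5.3.6. Describe 100 µg and 5 µg as amounts per injection. Confirm that every place that uses 0.45 mL agrees with the result: the summary table and sections 4.2, 5.3.6, 5.4.1 to 5.4.3, 5.6 and 6.3.3. Which figure is right is for the sponsor and the product provider to decide.

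The cost is a document check and a wording correction.
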